# Self-managed occupational therapy and physiotherapy for adults receiving inpatient rehabilitation (‘My Therapy’): protocol for a stepped-wedge cluster randomised trial

**DOI:** 10.1186/s12913-021-06462-9

**Published:** 2021-08-13

**Keywords:** Rehabilitation, Occupational Therapy, Physiotherapy, Physical Therapy, Intensity, Self-management, Implementation, Economic, Independence, Exercise

## Abstract

**Background:**

Ensuring patients receive an effective dose of therapeutic exercises and activities is a significant challenge for inpatient rehabilitation. My Therapy is a self-management program which encourages independent practice of occupational therapy and physiotherapy exercises and activities, outside of supervised therapy sessions.

**Methods:**

This implementation trial aims to determine both the clinical effectiveness of My Therapy on the outcomes of function and health-related quality of life, and cost-effectiveness per minimal clinically important difference (MCID) in functional independence achieved and per quality adjusted life year (QALY) gained, compared to usual care. Using a stepped-wedge cluster randomised design, My Therapy will be implemented across eight rehabilitation wards (inpatient and home-based) within two public and two private Australian health networks, over 54-weeks. We will include 2,160 patients aged 18 + years receiving rehabilitation for any diagnosis. Each ward will transition from the usual care condition (control group receiving usual care) to the experimental condition (intervention group receiving My Therapy in addition to usual care) sequentially at six-week intervals. The primary clinical outcome is achievement of a MCID in the Functional Independence Measure (FIM™) at discharge. Secondary outcomes include improvement in quality of life (EQ-5D-5L) at discharge, length of stay, 30-day re-admissions, discharge accommodation, follow-up rehabilitation services and adverse events (falls). The economic outcomes are the cost-effectiveness per MCID in functional independence (FIM™) achieved and per QALY gained, for My Therapy compared to usual care, from a health-care sector perspective. Cost of implementation will also be reported. Clinical outcomes will be analysed via mixed-effects linear or logistic regression models, and economic outcomes will be analysed via incremental cost-effectiveness ratios.

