### Setting and participants

The project will take place within eight rehabilitation wards (totalling over 200 rehabilitation beds) across four Victorian health networks (see anzctr.org.au for study sites). At one health service, the two wards will incorporate home-based bed-substitution; all others will be located within inpatient facilities. We will include all patients aged 18 years or older undergoing rehabilitation on the selected rehabilitation wards during the trial period, of any rehabilitation diagnosis. Patients who do not speak English and those with a cognitive impairment will not be excluded. We will exclude any patients without coverage under Australia’s universal health care program (Medicare).

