### Outcomes

#### Clinical evaluation

The primary clinical outcome is *functional independence*, which will be assessed using the Functional Independence Measure (FIM™) [37, 38]. The change in FIM™ from admission to discharge will be reported as the pro-portion of patients who achieve a MCID in FIM™ (22 points) [37]. The FIM™ is routinely recorded on admission and discharge from rehabilitation by accredited assessors, and will be used to report an overall score and sub-categories of motor and cognitive function.

Secondary outcomes include change in *health-related quality of life*, assessed using the EQ-5D-5L [39]; *rehabilitation length of stay*, reported as the number of overnight stays between the rehabilitation admission and discharge dates; *days at home up to 30 days after surgery (DAH30)* for any surgical patients [40, 41]; hospital re-admissions to the same health service one month (30 days) post-discharge (yes/no); discharge accommodation, categorised as home, transitional care, residential care, hospital, or death (no accommodation); need for post-discharge rehabilitation services (yes/no); and adverse events (falls), assessed as the number of falls and the number of serious falls during the rehabilitation admission, and these will be classified as occurring during or not during My Therapy participation.

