#### Statistical analyses

Analyses will only include data from patients who were admitted and discharged during the ward’s control condition period or experimental condition period. Patients still admitted to the rehabilitation wards at the end point of the study will not be included. It is expected that due to the step-wedged design, this will equally exclude long-stayers in the control and experimental condition periods. Each analysis will use individual patient-level data, clustered within the ward, and will use the length of time (in weeks) of experimental exposure as an effect modifier [32]. Length of time of exposure to the experimental condition is an important consideration when an intervention may take time to settle into usual practice and where there may be a cumulative effect [32]. Analyses will be conducted on an intention-to-treat basis.

The analyses will compare the FIM™ and the health-related quality of life utility index score between the control and the intervention groups. Health-related quality of life scores from the EQ-5D-5L will be converted from raw scores to a utility index based on an Australian population [46, 47]. The proportion of people who achieve a MCID of 22 points in FIM™ [35, 37] will be analysed using mixed effects logistic regression, and the change in FIM™ score and utility index will be ana-lysed using mixed effects linear regression. Length of stay will also be analysed via a linear regression model.

While not powered for a secondary analysis, there will be an exploratory secondary analysis of the same outcome measures within each of the clusters and for the two home-based bed-substitution wards. Other secondary outcomes will be compared between groups using univariable analyses. All outcomes will be reported with 95% confidence intervals and analyses will assume a significance of *p* < 0.05.

For the economic evaluation, the primary outcome will be presented as cost-effectiveness and cost-utility analyses, reporting (i) the cost per MCID in FIM™ achieved; and (ii) the cost per QALY gained. Costs will include the rehabilitation length of stay, acute transfers within the rehabilitation stay and unplanned re-admissions within the 30 days post discharge. The QALYs will be calculated using the utility index scores.

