## Limitations

While My Therapy aims to improve patient outcomes by increasing the therapy delivered, it does not attempt to differentiate the relative contribution of increased time dedicated to independent practice and the time spent with the therapist. In addition, My Therapy does not evaluate whether skilled therapists can teach a patient to practice safely, independently, and often. Future trials will need to ascertain how practice and therapy independently contribute to patient outcomes; where practice is the amount of time performing an exercise, task or activity [54], and therapy is the time spent with a professionally qualified therapist who educates patients, co-designs their goal-directed program, teaches them how to perform an activity, gives feedback, helps patients to practice and structures a learning environment [54], My therapy also includes teaching patients how to undertake an activity independently and enabling them to implement what they have learned in daily life [54].

There are also practical and operational issues which may potentially impact study procedures and outcomes. Each of these has been carefully considered, with *a priori* mitigation strategies put in place. Within trial sites, independent therapy prescription may already be practiced, to some extent, as part of usual care conditions. As such, there may be variability in clinicians’ receptiveness to implementing My Therapy and potential differences in effect sizes across trial sites. While My Therapy is still expected to differ substantially to usual practice, a full process evaluation (described in the Process Evaluation Protocol [36]). will be conducted to better understand these contextual factors. Another consideration relates to the inclusion of two ‘virtual’ home-based bed-substitution rehabilitation wards. While not initially planned, this change in practice at one of the included health networks presents a good opportunity for sub-group analyses, comparing the impact of My Therapy in traditional inpatient wards to home-based wards, which are becoming increasingly common in Australian hospitals.

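### Discharge accommodation is defined by destination alone and compared univariably, so returning residential-care residents cannot be told apart from new placements and ward mix can enter the contrast

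*Protocol article*

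**What the plan says.** The abstract names the outcome without defining it, in the list "30-day re-admissions, discharge accommodation, follow-up rehabilitation services and adverse events (falls". The definition is in the Clinical evaluation section: "discharge accommodation, categorised as home, transitional care, residential care, hospital, or death (no accommodation". Nothing in the article refers to accommodation before admission or to return to usual residence.

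Eligibility under Setting and participants is wide: "all patients aged 18 years or older undergoing rehabilitation on the selected rehabilitation wards during the trial period", of any rehabilitation diagnosis. The one exclusion is "We will exclude any patients without coverage under Australia’s universal health care program (Medicare". People who already live in residential care can therefore enter. The same section says "At one health service, the two wards will incorporate home-based bed-substitution; all others will be located within inpatient facilities".

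For analysis, the Statistical analyses section gives FIM, utility index and length of stay regression models, and then says "Other secondary outcomes will be compared between groups using univariable analyses". Discharge accommodation falls in that remainder. The section also plans an "exploratory secondary analysis of the same outcome measures within each of the clusters and for the two home-based bed-substitution wards", and the Limitations section speaks of sub-group analyses "comparing the impact of My Therapy in traditional inpatient wards to home-based wards".

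**The concern.** Function and quality of life are both analysed as change from admission. Discharge accommodation is recorded as a status with no starting point. For a patient who lived in residential care before the illness, a return there may be the best result available. For a patient who lived at home, the same code means loss of independent living. My Therapy could plausibly prevent some of the second kind of discharge. It can do little about the first, so pooling the two hides part of any effect.

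The second issue is setting. Patients treated at home are probably discharged home much more often than patients on inpatient wards. In a stepped-wedge trial each ward contributes to both conditions, but in proportions set by its crossover position. Unless the analysis accounts for ward, a difference in ward mix between conditions can look like a treatment effect or mask one.

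What is at stake is how readable one secondary outcome will be.

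**Working it through.** The article gives no rate, effect size or sample size for this outcome, so there is no stated figure to reproduce. Both calculations below are illustrations on assumed rates.

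**1. Returning residents mixed with new placements**

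Assumptions, none of them in the article: a share f = 0.03 to 0.10 of patients is admitted from residential care; 90% of these return; a share n = 0.03 to 0.08 of all other patients is newly placed; My Therapy cuts new placements by 30% (true risk ratio 0.70).

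- Residential-care discharges = 0.9f + (1 − f)n
- Share that is unchanged residence = 0.9f / [0.9f + (1 − f)n]
- Observed risk ratio = [0.9f + 0.70(1 − f)n] / [0.9f + (1 − f)n]

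Mildest case, f = 0.03 and n = 0.08: the parts are 0.027 and 0.0776, total 0.1046. Unchanged share = 0.027 / 0.1046 = 0.26. Observed risk ratio = (0.027 + 0.0543) / 0.1046 = 0.78.

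Strongest case, f = 0.10 and n = 0.03: the parts are 0.090 and 0.027, total 0.117. Unchanged share = 0.090 / 0.117 = 0.77. Observed risk ratio = (0.090 + 0.0189) / 0.117 = 0.93.

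The dilution is much milder if the contrast is made on discharge home. If 5%, 10% or 15% of patients come from residential care and all return there, a true gain of 5 percentage points among the others appears as 5 × 0.95 = 4.75, 5 × 0.90 = 4.5 or 5 × 0.85 = 4.25 points.

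**2. Ward mix in a crude comparison**

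From the article: eight wards, nine six-week blocks, two wards with home-based bed-substitution. Assumed: one ward crosses per block (the timeline figure is not shown in the text at hand) and every ward-block has the same number of patients.

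The ward that crosses k-th gives k control blocks and 9 − k intervention blocks. Control blocks total 1 + 2 + … + 8 = 36, and intervention blocks total 72 − 36 = 36. If the home-based wards cross a-th and b-th:

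- share of control patients from these wards = (a + b)/36
- share of intervention patients from these wards = (18 − a − b)/36
- shift in the crude proportion discharged home, with no treatment effect = (intervention share − control share) × (proportion home in home-based wards − proportion home in inpatient wards)

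At positions 1 and 2 the shares are 3/36 = 8.3% of control and 15/36 = 41.7% of intervention, a difference of 33.3 points. At positions 7 and 8 the difference is the reverse.

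| Assumed proportion home: home-based / inpatient | Largest shift |
|---|---|
| 0.95 / 0.75 | ±0.333 × 0.20 = ±6.7 points |
| 0.95 / 0.85 | ±0.333 × 0.10 = ±3.3 points |

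These are extremes. When a + b = 9 the shares are equal and the shift is zero. Over the 28 possible pairs of positions, the shares differ by more than 10 points in 18 (64%).

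**The case against.** A reader might infer that the trial counts residents who return to care as poor outcomes. The article does not support that. The five categories carry no ranking and no split into success and failure. The loss is only that two different events share one code.

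A reader might also infer that patients on the home-based wards are recorded as home by default, or that treatment setting is ignored. Neither is stated. These patients can still be discharged to any of the other categories, and wards that incorporate bed-substitution need not treat every patient at home throughout. The article plans exploratory analyses of these wards. What stays open is whether they cover this outcome: the phrase about the same outcome measures follows FIM, utility and length of stay, and comes before the sentence on other secondary outcomes.

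The ward-mix argument depends on the comparison being truly crude. The Statistical analyses section also says that each analysis uses patient data clustered within ward, and the abstract says that clinical outcomes are analysed by mixed-effects models. Under a model with ward and period terms most of the setting effect would go. The single sentence on univariable analyses does not sit easily with these two statements, and they need reconciling.

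Two further objections have weight. Return to previous residence is not among the trial's stated aims, so asking for it goes beyond correcting an error. And an article need not list every data field: usual accommodation may already be collected. Both limit the point. They do not remove it, because the article does fix the categories and the form of analysis, and these two choices together cause the loss.

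**Conclusion.** The point holds as a modest improvement to a secondary outcome. As defined, the outcome cannot separate a resident's return to residential care from a new placement, and a univariable comparison leaves ward mix uncorrected.

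On the assumed rates, a true risk ratio of 0.70 for new placement would be seen as 0.78 to 0.93, and ward mix could move a crude proportion discharged home by up to 3.3 to 6.7 percentage points at the extreme crossover orders. The direction of these results is secure. Their size rests on care-home shares, placement rates and discharge-home rates that the article does not give, and on one ward crossing per block with equal ward sizes. The primary outcome and its conclusion are not affected.

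**What to change.** - Keep the five destination categories as a descriptive table by condition.
- Take usual accommodation before admission from the medical record, if it is not already collected.
- Make the compared outcome new residential-care placement among patients not admitted from residential care. An alternative is discharge to the same or more independent accommodation than before admission (yes/no), with death and discharge to hospital as no.
- Analyse it with ward and period terms, in line with the mixed-effects models named in the abstract, and reword the sentence on univariable analyses to agree.
- State that the planned analysis of the two home-based wards covers this outcome.

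The cost is at most one more field from records that are already being abstracted into REDCap, plus a few lines of wording. The restricted comparison loses the patients admitted from residential care: on the assumed 3-10%, that is 0.03 × 2,160 ≈ 65 to 0.10 × 2,160 = 216 of the planned sample.

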**Discussion:**

The My Therapy implementation trial will determine the effect of adding self-management within inpatient rehabilitation care. The results may influence health service models of rehabilitation including recommendations for systemic change to the inpatient rehabilitation model of care to include self-management. Findings have the potential to improve patient function and quality of life, and the ability to participate in self-management. Potential health service benefits include reduced hospital length of stay, improved access to rehabilitation and reduced health service costs.

**Trial registration:**

This study was prospectively registered with the Australian and New Zealand Clinical Trials Registry (ACTRN12621000313831; registered 22/03/2021, http://www.anzctr.org.au/Trial/Registration/TrialReview.aspx?id=380828&isReview=true).

## Background

Globally, inpatient rehabilitation costs are substantial. In the UK, there are 2.2 million NHS-funded inpatient rehabilitation admission across Complex Specialised, Specialist and Non-specialist Services annually, which cost the NHS £858 million (GBP 2018/19) [1, 2]. In the US, Medicare is the main insurer for inpatient rehabilitation within skilled nursing facilities [3] and intensive rehabilitation within hospital settings [3, 4]. There are 2.5 million funded skilled nursing facilities admissions [3] and 408,000 hospital inpatient rehabilitation admissions annually [4, 5] $28 billion (USD 2016) [4, 5] $8 billion (USD 2018) [$1.2 billion (AUD 2015/16) annually [6–8]. There is also evidence that the cost and demand for inpatient rehabili-tation is increasing [9]. This growth is thought to be driven by the ageing population, increasing survival fol-lowing acute illness and injury, greater comorbidity in patients, and higher expectations of recovery within the general population [9].

Rehabilitation is defined as “a process whereby a person who has continuing problems arising from an illness is helped both to reduce the extent of their difficulties and to use whatever personal strengths and skills they have, so that they can achieve goals of importance to them, both in the shorter term and, more importantly, in the longer term” [10]. Effective rehabilitation interventions include exercise, practice of tasks, education and self-management by the patient [11]. Clinical guidelines for general adult inpatient rehabilitation recommend three or more hours of therapy per weekday in addition to weekend therapy as tolerated [12]. Rehabilitation recommendations for specific cohorts, such as patients post-stroke, vary between one and a half and three hours per day for occupational therapy and physiotherapy participation [13, 14]. However, there is an evidence-practice gap and many services provide far less than the recommended amount [15–17]. Receiving less therapy than is recommended may be the reason patients may fail to achieve an optimal outcome in their recovery from injury, illness, or disease [18]. The low activity level in rehabilitation can also lead to patients feeling disempowered, bored and frustrated [19], where they spend most of the day sitting and lying down [20, 21].

While funding additional staff to increase the amount of supervised occupational therapy and physiotherapy could be an option [22], limited financial resources are often a barrier to implementation [23]. An alternative is to effectively increase the dose of inpatient rehabilitation by engaging patients in self-management through independent practice of occupational therapy and physiotherapy exercises and activities, outside of supervised therapy sessions.

My Therapy is a self-management program whereby the patient is educated and empowered to complete additional practice in-between therapist supervised sessions, during their episode of inpatient rehabilitation [24]. My Therapy involves goal-setting which is completed by both the patient and the therapist; patient education, motivation and empowerment; in addition to independent self-practice. While the My Therapy goals inform the individually tailored exercises and activities recommended by the therapist, it is the patient who decides which exercises and activities are practiced, and how much they are practiced each day.

While the definition of self-management in the literature is unclear and at times contentious [25], My Therapy defines self-management as a component of care which facilitates behaviour change and allows people to develop the skills to work with their problems or challenges, identify and contribute towards their own goals and ultimately become responsible for their own rehabilitation and health [26, 27]. Self-management includes education and advice about the condition, is built on the patient’s own goals and equips patients to make decision about their health [28]. Achieving self-practice within a self-management program is dependent on motivation, including intrinsic patient motivation and the therapists ability to motivate the patient, as well as the severity of the condition [29].

To differentiate My Therapy from general therapist advice and education regarding self-practice during inpatient rehabilitation and goal setting with the patient, My Therapy must also adhere to the following criteria (a) a written program, (b) therapist documentation of the program within the medical record, (c) include a feedback mechanism to the therapist (e.g., a paper based or smart device tick sheet), and (d) be actively monitored and progressed as clinically required. My Therapy is tailored to individual needs, recommended by the patient’s treating occupational therapist and physiotherapist after goal setting with the patient, and can be practiced within business hours, in the evenings or over the weekend.

A recent pilot study showed the implementation of My Therapy to be feasible in hospitalised older people with musculoskeletal conditions and frailty (n = 116) [24]. The pilot study led to around 100 min of extra weekly practice alongside usual care rehabilitation and the benefits occurred without additional staff or adverse events [24]. Compared to usual care, more than double the proportion of patients allocated to My Therapy achieved a minimal clinically important difference (MCID) in functional independence from admission to discharge [24], and it was also delivered safely in those with cognitive impairment.

The current protocol builds on this initial pilot study [24]. The project will scale-up implementation of My Therapy across inpatient and home-based rehabilitation wards in Australian public and private health networks, and evaluate the benefits and cost-effectiveness of My Therapy via a stepped-wedge cluster randomised trial design. This trial aims to determine the effectiveness of My Therapy on clinical outcomes of function and health-related quality of life, when implemented across four health networks. It will also determine the cost-effectiveness per MCID in functional independence achieved and per quality adjusted life year (QALY) gained compared to usual care; in addition to the cost of implementation. We hypothesise that My Therapy will result in improved functional independence and health-related quality of life during rehabilitation without adverse events (falls); and will be cost-effective to the health service due to a reduction in rehabilitation length of stay, compared to usual care alone.

